### Risk factors

Data on individual risk factors from the 45 and Up Study questionnaire (eg. age, gender, socioeconomic status, disability), and health system characteristics from linked data (eg. prescriber, number of pharmacies and geographical region) will be obtained to identify factors associated with the likelihood of high risk prescribing.

### Ascertainment of outcomes

Data on a range of clinical outcomes will be obtained, including: hospitalisation (first admission to hospital, total days in hospital, cause-specific hospitalisation, covering falls-related hospital admission, and fracture-related hospital admission); all-cause mortality; and, where possible, admission to institutionalised care and cause-specific mortality. Follow-up will be from the date of recruitment, to the last available data on hospitalisation, death or institutionalisation, whichever occurs first. The 45 and Up Study recruitment was from February 2006 to April 2009, giving a range of follow-up duration of 2–5 years, by end 2012 (accounting for linked data delays).

### Health interventions

Changes in high risk prescribing will be evaluated in relation to two health interventions: the Home Medicines Review [35], and the Chronic Disease Management [36] item of the MBS. The Home Medicines Review is a Commonwealth-funded service introduced in 2001. It is a free collaborative medication management service provided to the patient. The collaborative service involves the patient, their primary physician and pharmacist, whereby the pharmacist referred by the patient’s general practitioner conducts an interview with the patient and generates a written report for the primary physician to discuss the medication management plan with their patient. The Chronic Disease Management program was introduced in 2005 to enable primary care physicians to plan and coordinate the health care of patients with chronic or terminal medical conditions. A ‘chronic medical condition’ is one that has been or is likely to be present for at least six months, including but not limited to asthma, cancer, cardiovascular disease, diabetes mellitus, musculoskeletal conditions and stroke.

### Economic analysis

The cost analysis will be undertaken from a health system perspective. Total annual health system costs will be estimated overall and for each type of health care resource utilisation for each individual in the 45 and Up Cohort, based on their hospital, Medicare and pharmaceutical utilisation data. Costs will be assigned to each type of resource utilisation based on standard Australian sources (for example, using the PBS and MBS for pharmaceutical and medical services, national Australian Refined Diagnosis Related Groups cost weights for inpatient services and standard ambulatory costs for outpatient and emergency department visits). Differences in total and average annual costs will be estimated for the high-risk and non-high risk prescribing groups using each of the definitions of high risk prescribing. Covariates will be included in the cost equations and interacted with a dummy variable for the high risk prescribing group. Differences in total health care costs and for each type of health care resource utilisation will be estimated.

### Statistical analysis

The statistical analysis will be conducted using the standard pharmaco-epidemiological methods including descriptive analysis, univariate and multivariate regression analysis (eg. Cox regression modelling, negative binomial or Poisson regression), time-varying methods, and controlling for relevant confounding factors using a number of different approaches (eg. stratification by disease, propensity scores modelling).

To answer the first study objective, analysis will be performed to calculate the high risk prescribing indicators, using the 45 and Up Study cohort, linked to PBS data and restricted to concession card holders. The patterns of high risk prescribing will be summarised using proportions and means. To answer the second and third objectives, analysis will be performed to identify individual and health system based risk factors for high risk prescribing, using the same dataset in aim one. Univariate and multivariate analysis with relevant covariates will be used to quantify the risk for high risk prescribing compared to age and gender-matched controls. Using the same dataset, linked to other data sources, we will investigate the relationship of high risk prescribing indicators with hospitalisations, deaths and institutionalisation, allowing for a range of factors. Analysis related to the fourth objective – calculation of the economic costs and implications of high risk prescribing to the health care system – will be performed as outlined in the previous section. To answer the fifth objective, we will perform the analysis to evaluate the possible impact of policy-related interventions on high risk prescribing. In particular, we will compare the rates of high risk prescribing in participants with and without these interventions and the incidence of high risk prescribing before and after each of these interventions, within individuals.

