## Background

In older adults, high risk prescribing can be defined as prescribing likely to lead to adverse clinical outcomes or prescribing that does not align with quality use of medicines principles. A range of indicators have been proposed to quantify high risk prescribing in older people. These include multiple medication use or polypharmacy, potentially inappropriate prescribing and exposure to high risk medicines, measured using different risk assessment tools.

Although the concomitant use of multiple medicines is often indicated in the treatment and prevention of health problems, polypharmacy is generally considered as high risk prescribing in older adults, and is associated with increased risk of harm [1-3], including adverse drug reactions, falls, hospitalisation, institutionalisation, and mortality [1]. Polypharmacy (concomitant use of ≥ 5 medicines) is common in older adults, and is estimated to be present in around half of Australians aged 65–74 years, and two-thirds of those aged ≥75 years [4]. The prevalence of “hyperpolypharmacy” (concomitant use of ≥ 10 medicines) in community-dwelling older adults has been reported to range from 5% to 26% [5,6].

High risk prescribing also includes potentially inappropriate prescribing, defined as the use of medicines whose potential harms to older adults may outweigh the benefits [7]. Potentially inappropriate prescribing can be assessed using explicit and implicit approaches. The Beers Criteria, an explicit USA consensus list is the most widely used indicator to define potentially inappropriate prescribing [7,8]. The associations between Beers Criteria and outcomes have been investigated across a range of populations and settings of older adults, with mixed findings being reported across studies [9]. Despite the efforts to improve the quality use of medicines in this population, recent systematic review suggests that potentially inappropriate prescribing is still common in older people [10].

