High risk prescribing may also encompass exposure to “high-risk” medicines such as those with anticholinergic and sedative properties. A number of anticholinergic and/or sedative scores have been developed to capture the cumulative exposure to these pharmacological classes [2]. One such tool is the Drug Burden Index (DBI), a pharmacological score based on the principles of dose–response and cumulative effect, that measures an individual’s total exposure to medicines with anticholinergic and sedative effects [11]. In studies of older people, the prevalence of exposure to DBI medicines ranged from 29–70% [12,13]. Increasing DBI score has been associated with a higher risk of a range of adverse clinical outcomes, including functional impairment, frailty, falls and hospitalisation in populations of older adults from the USA, Australia and Europe [11-19].

Strategies to reduce high risk prescribing, including pharmacist-conducted medication reviews, educational interventions and policy approaches, have been trialled in older adults [20-22]. However, the success of these interventions has been limited. To reduce the likelihood of clinically significant adverse outcomes, rational withdrawal of medications may be the appropriate clinical decision and may result in significant clinical benefits in some older people with high risk prescribing [23]. To date, real-world approaches to reduce polypharmacy in older people have generally not been successful [22,24]. While interventional approaches can reduce medication exposure in older adults, the evidence for their clinical effectiveness and sustainability is conflicting [24].

The current evidence from pharmaco-epidemiological studies suggests that high risk prescribing increases the risk of adverse outcomes in older adults [1,2]. However, there is a lack of reliable evidence at the population level on the prevalence and outcomes relating to high risk prescribing in older people. Moreover, evidence is required regarding the impact of pragmatic medicines-related interventions aimed at improving medication management in older adults. The aims of this project are to determine the prevalence, risk factors, clinical implications and costs of high risk prescribing, and the impact of interventions on high risk prescribing in older people within a large population-based cohort study; specifically to:

1) Estimate the prevalence of high risk prescribing;

2) Investigate the risk factors for high risk prescribing;

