### The 45 and Up study cohort

The 45 and Up Study cohort includes 267,153 men and women aged 45 and over from the state of NSW, Australia, randomly sampled from the Medicare Australia database [25]. Participants completed a self-administered postal questionnaire and provided signed consent for participation and follow-up, including linkage to health records (including data on deaths, hospital admissions, and aged care admissions). Recruitment was conducted from February 2006 to April 2009, with an 18% response rate. Following exclusion of individuals with missing data on age and sex, 266,074 participants remained. Of these, 143,199 (54%) are aged 60 years and over (Table 1). Overall, 28% (n = 73,528) of the cohort reported holding a healthcare concession card, hereafter referred as concession card holders. This status will also be confirmed using the health administrative databases. For the purposes of the High Risk Prescribing project, the study sample will be restricted to cohort members who are concession card holders, as this allows full capture of health care utilisation.

**Table 1 T1:** Characteristics of the concession card holders in the 45 and Up study, and total study population

**Characteristic**^ **~** ^	**Concession card holders (n = 73,528; 28%)**	**All participants (n = 266,074)**

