### Sample size

Using data available to the end of 2012, the project will be highly powered for the main outcomes, with the ability to detect a minimum relative risk of death (the least common outcome) of 1.12, for each of the three high risk prescribing indices (assuming the following prevalences: DBI 48%; Beers 20% and polypharmacy 30%) [5,15], at 5% significance and 80% power. The incidence of total hospitalisation and hospitalisation for falls and fractures will be greater than the incidence of death, and hospitalisation for adverse drug reactions is similar to the incidence of death. To investigate the relationship between MBS interventions and outcomes, the linkage will be updated annually to increase power. An estimated 5% of people aged ≥ 65 have had a Home Medicines Review; however we are not able to locate estimates for other MBS review items. Assuming 5% exposure over the study period, for the smallest high risk prescribing stratum (Beers: 20%) this would allow detection of a relative change in prevalence of 0.05, comparing *before* and *after* the intervention.

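### Aim 2 names age and gender as risk factors, but its stated comparison uses age- and gender-matched controls and so cannot estimate either

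*Protocol article*

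**What the plan says.** Aim 2, at the end of the Background section, is to "Investigate the risk factors for high risk prescribing". The Risk factors section says what will be examined: "Data on individual risk factors from the 45 and Up Study questionnaire (eg. age, gender, socioeconomic status, disability", together with health system characteristics. These data "will be obtained to identify factors associated with the likelihood of high risk prescribing". Age and gender are the first two examples given.

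The Statistical analysis section describes the corresponding analysis. It will "identify individual and health system based risk factors for high risk prescribing, using the same dataset in aim one", and univariate and multivariate analysis with relevant covariates will "quantify the risk for high risk prescribing compared to age and gender-matched controls". No matching ratio, method or reason for matching is given. The aim 1 dataset is the cohort linked to PBS data and restricted to concession card holders; the cohort section reports that "28% (n = 73,528) of the cohort reported holding a healthcare concession card".

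**The concern.** A factor used for matching has the same distribution in both groups by construction, so its association with group membership is removed. If people with high risk prescribing are compared with age- and gender-matched people without it, the comparison cannot show how high risk prescribing varies with age or gender. Reading controls the other way, as people without a given risk factor matched on age and gender to people with it, removes the same two effects.

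Matching usually pays when data on controls are costly to collect. Here they are not: the account of the Commonwealth linkage says PBS and MBS data for all participants are already joined to the questionnaire. Matching therefore gains nothing in data collection and may leave usable people out. At stake is whether aim 2, carried out as written, can report on two of the factors it names.

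**Working it through.** The article gives no sample size or power figure for aim 2, so there is none to reproduce. Two checks apply.

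**1. Can the matched comparison estimate age and gender?** By construction it cannot estimate their main effects; only interactions with them remain estimable. A simulation illustrates this. It used the age groups of Table 1 for card holders (14,888 + 25,599 + 20,432 + 12,609 = 73,528) and the Table 1 share of women (40,773 of 73,528). The odds ratios were assumed, not taken from the article: 1.65 per age group, 1.35 for women, and 1.65 for one further binary factor. Indicator prevalence was set near 20% and near 30%.

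| Analysis | Age, odds ratio per group | Female, odds ratio |
|---|---|---|
| Assumed truth | 1.65 | 1.35 |
| Full-cohort regression | 1.66 to 1.67 | 1.34 to 1.36 |
| 1:1 matched, age and gender only | 1.00 | 1.00 |
| 1:1 matched, further factor added | 0.98 | 1.00 |

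The further factor survived matching (1.66 and 1.68), so the loss is confined to the matching factors.

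**2. What might matching cost in precision?** Inputs: N = 73,528 (cohort section); prevalence p of 20% for Beers, 30% for polypharmacy and 48% for DBI (Sample size section). The matching ratio 1:m is not stated, so it is varied.

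- People with the indicator: Np. People without it: N(1 − p).
- Controls used: at most the smaller of mNp and N(1 − p). The remaining controls are unused.
- Variance of a contrast is taken as proportional to 1/cases + 1/controls. Relative to the full cohort, while mp ≤ 1 − p, it is (1 + 1/m)(1 − p). The standard error ratio is its square root.

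At 1:1:

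- Beers: 14,706 with and 58,822 without; unused 44,117, or 60% of N. Variance ratio 2 × 0.80 = 1.60; standard error × 1.26.
- Polypharmacy: 22,058 with and 51,470 without; unused 29,411, or 40%. Variance ratio 2 × 0.70 = 1.40; standard error × 1.18.
- DBI: 35,293 with and 38,235 without; unused 2,941, or 4%. Variance ratio 2 × 0.52 = 1.04; standard error × 1.02.

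At other ratios:

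| Ratio | Beers unused (SE) | Polypharmacy unused (SE) | DBI unused |
|---|---|---|---|
| 1:2 | 40% (× 1.10) | 10% (× 1.02) | 0 |
| 1:3 | 20% (× 1.03) | 0 | 0 |
| 1:4 | 0 | 0 | 0 |

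The unused shares are minima, because they assume that every age and gender stratum can supply the controls asked of it.

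**The case against.** Several points on the other side have force.

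- A reader might infer that the project can say nothing about age and gender. The documents do not support that. The effects are lost only in the matched comparison. The cohort data remain intact, and aim 1 could tabulate prevalence by age and gender. Still, the article states no such tabulation, and no unmatched analysis of these factors under aim 2.
- A reader might infer that most of the cohort will be discarded. That depends on the unstated ratio and on the indicator. For DBI the loss is small even at 1:1, and at 1:4 there may be none for any indicator.
- A reader might infer that many of the oldest people would go unmatched, because the Background puts polypharmacy at "two-thirds of those aged ≥75 years". That is a national estimate from a cited source, not an assumption for this cohort, for which the article assumes 30% overall and gives no age-specific figure.
- A reader might object that odds ratios overstate risk when the outcome is common. The article mentions no odds ratio or logistic model, and it names Poisson regression among its examples, so that criticism does not apply.
- The sentence stands in text that covers the second and third objectives together, and matching on age and gender is ordinary for objective 3, where both are nuisance factors. The word matched may also have been meant as adjusted. But the sentence speaks of the risk of high risk prescribing itself, which is aim 2, and nothing in the text says that adjustment was meant.
- A condensed article may leave the matching ratio and model form to a fuller plan. That is accepted, and their absence is not the point. The article itself fixes the matching variables, and they conflict with its own list of risk factors.

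**Conclusion.** The conflict between the Risk factors and Statistical analysis sections is real. As written, the aim 2 comparison cannot estimate the main effects of age or gender, and the article states no other aim 2 analysis that would. This follows from the design and needs no assumption about effect sizes; the simulation only illustrates it.

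The precision cost is secondary and conditional. At 1:1 the standard error rises by about 26% for Beers, 18% for polypharmacy and 2% for DBI, and the rise could be nil at 1:4. These figures rest on the article's assumed prevalences, on 73,528 eligible card holders (a self-reported count still to be confirmed from administrative data), and on enough controls in every stratum. Other risk factors can still be estimated under matching. No data are irretrievably lost, because the linked cohort stays available for an unmatched model.

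**What to change.** For aim 2, replace the matched-control comparison with regression on all eligible concession card holders, with age in a flexible form and gender as covariates, and report the estimates for both alongside the other risk factors. Prevalence ratios are preferable and can come from the Poisson regression already named, with robust variance. Keep matching on age and gender to analyses where the two are nuisance factors, such as the outcome analyses of aim 3, and say so.

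The cost is about one sentence in the Statistical analysis section. No new data or linkage is needed, because multivariate regression on the same dataset is already planned.

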3) Quantify the relationship of high risk prescribing to adverse health outcomes;

4) Determine whether associations between high risk prescribing and adverse outcomes vary according to individual and/or health care system specific factors;

5) Calculate the economic cost and implications of high risk prescribing to the health care system;

6) Investigate whether certain routine medicines-related interventions, including the Home Medicines Review and Chronic Disease Management are associated with reductions in high risk prescribing.

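### The intervention aim rests partly on a before-after comparison with no concurrent comparator, measured by incidence although the aim asks about reductions and the detectable change is stated in prevalence

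*Protocol article*

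**What the plan says.** The sixth aim in the Background asks whether the two routine interventions "are associated with reductions in high risk prescribing". The Statistical analysis section counts this as the fifth objective and names two contrasts for it. One is to "compare the rates of high risk prescribing in participants with and without these interventions". The other is "the incidence of high risk prescribing before and after each of these interventions, within individuals".

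The opening paragraph of that section lists methods for the project as a whole, including time-varying methods and "controlling for relevant confounding factors using a number of different approaches (eg. stratification by disease, propensity scores modelling". It does not tie them to the intervention aim.

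The Health interventions section says that the Home Medicines Review follows referral by the general practitioner, and that Chronic Disease Management serves patients with chronic or terminal conditions. The Sample size section assumes 5% exposure and a Beers prevalence of 20%, and claims "detection of a relative change in prevalence of 0.05", before against after.

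**The concern.** A comparison of recipients with themselves counts every change around the index date as effect. Two such changes are expected here without any intervention effect.

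- **Regression to the mean.** If people tend to be referred when their prescribing is at a high point, it will tend to be lower afterwards.
- **Drift.** Medicine use rises with age and illness. The Background puts polypharmacy at around half of Australians aged 65–74 and two-thirds of those aged 75 and over. These are cross-sectional figures, so they give a direction but no yearly rate.

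The two act in opposite directions, and the before-after contrast cannot separate either from a real effect. The with/without contrast has a comparator, but if it is left unadjusted it tends to show more high risk prescribing in recipients.

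The measure is a second problem. With incidence as new onset, a person who was exposed before the review and stops afterwards is not counted, although that is the reduction the aim asks about. The sample size statement uses prevalence, so the article gives two measures for the same contrast.

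**Working it through.** **1. The article's own figure.** Inputs: 73,528 concession card holders; 5% exposed, so 0.05 × 73,528 = 3,676; Beers prevalence 20%; relative change 0.05, read as 20% to 19% (d = 0.01). The 5% significance and 80% power are stated for death and assumed to carry over; the test is taken as two-sided.

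- Unpaired: SE = √[(0.20×0.80 + 0.19×0.81)/3,676] = 0.00924; d/SE = 1.08; power about 19%.
- Paired (McNemar), within-person correlation ρ: discordant share = 0.314 − 0.3138ρ; pairs needed ≈ 7.85 × discordant share / 0.01². At ρ = 0.70 this is about 7,400; at 0.80 about 4,940; at 0.85 about 3,710; at 0.90 about 2,470.

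The stated 0.05 is therefore reachable with 3,676 pairs only if ρ is about 0.85 or more. The article gives no ρ.

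**2. Regression to the mean with no intervention effect.** Assumptions that are not in the article: stable population prevalence p = 0.20; receipt depends on current Beers status only; recipients' pre-intervention prevalence is q; correlation between windows is ρ.

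P(positive after | positive before) = p + (1−p)ρ and P(positive after | negative before) = p(1−ρ). Hence post = p + ρ(q−p), and the relative fall = (1−ρ)(q−p)/q.

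Example with q = 0.30, ρ = 0.85: 0.30×0.88 + 0.70×0.03 = 0.285, a fall of 0.015/0.30 = 5.0%.

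| ρ | fall, q = 30% | fall, q = 40% |
|---|---|---|
| 0.70 | 10% | 15% |
| 0.85 | 5.0% | 7.5% |
| 0.90 | 3.3% | 5.0% |
| 0.95 | 1.7% | 2.5% |

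Solving pk/(pk+1−p) = q, a q of 30% means that Beers-positive people are k ≈ 1.7 times as likely to receive the intervention; 40% means k ≈ 2.7. With weak selection (k = 1.1, q = 21.6%) the fall is 2.2% at ρ = 0.70 and 0.7% at ρ = 0.90.

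**3. A stably higher level.** If recipients regress to their own long-run level m rather than to 20%, the fall is (1−ρ)(q−m)/q. With q = 0.30, m = 0.25, ρ = 0.85 it is 0.15×0.05/0.30 = 2.5%. With m = q it is zero.

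**4. Significance without a true effect.** A fall below 5% can still test as significant. Take k = 1.5 (q = 27.3%) and ρ = 0.90. Discordant shares are 0.273×0.08 = 0.0218 and 0.727×0.02 = 0.0145, so d = 0.0073 (a 2.7% fall) and the total is 0.0364. With 3,676 pairs, (0.0073×√3,676 − 1.96×√0.0364)/√(0.0364 − 0.0073²) ≈ 0.35, so a significant result occurs about 64% of the time, against a nominal 5%.

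**5. The two contrasts side by side.** For q = 0.30 and ρ = 0.85, recipients are at 28.5% afterwards and non-recipients at (0.20 − 0.05×0.285)/0.95 = 19.6%. Unadjusted, the with/without table suggests harm and the before-after table suggests benefit, although the true effect is nil.

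**6. The measure.** The aim speaks of reductions, Statistical analysis of rates and of incidence, and Sample size of prevalence. Only the last fits the detectable change that is quoted.

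**The case against.** The strongest reply is that the article plans more than a crude before-after table. It pairs that contrast with a comparator group, lists propensity scores, stratification and time-varying methods for the whole project, and words the aim as association. A journal article also leaves index dates, windows and matching to the full plan. Much of this stands. The listed methods may make the with/without contrast fair, and absent detail is not the complaint. None of it gives the within-person contrast a comparator, and that contrast is a stated choice.

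Four stronger readings are tempting, and the article does not support them.

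- A reader might infer that regression to the mean will produce the 5% change. That depends on selection strength and correlation, and neither is given. At ρ = 0.95 no degree of selection reaches 5%, because the ceiling is (1−0.95)×(1−0.20) = 4%. Upward drift would offset part of any fall.
- A reader might infer that recipients are selected on the prescribing being measured. The article states referral and chronic illness; it gives no criterion based on prescribing. Selective receipt is a fair inference, but selection on current Beers status is an assumption.
- A reader might say the study is sized on 5%. The cohort is fixed, and 0.05 is a claimed detectable change.
- A reader might treat incidence as plainly the wrong measure. The article does not define it, and its medicine count and Drug Burden Index could show reductions. The conflict with prevalence remains whichever definition is meant.

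**Conclusion.** The point holds for the before-after contrast and for its measure. Followed as written, that contrast can give a wrong answer to the sixth aim in either direction when the true effect is nil, and no rule is stated for reading it when it disagrees with the with/without comparison. The missing comparator and the clash between incidence and prevalence are visible in the text and need no assumption.

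The size does need assumptions. Under selection on current Beers status, the false relative fall runs from 1.7% to 10% for a pre-intervention prevalence of 30%, and from 2.5% to 15% for 40%, as ρ goes from 0.95 down to 0.70. It is smaller with weaker selection or if recipients have a stably higher level. It can match or exceed the claimed detectable 5%, but need not.

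**What to change.** Make the main analysis of the sixth aim a controlled before-after comparison (difference-in-differences). Compare recipients with concurrent not-yet-recipients who are given the same index date and are comparable on age, gender and disease, and allow for clustering by person.

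Check parallel trends over several windows before the index date. Show results with and without matching on the prior level of the indicator. Without such matching, regression specific to recipients may remain; with it, regression can be induced in the comparators if recipients have a stably higher level. The earlier windows help to show which applies.

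Replace incidence by prevalence, add discontinuation among those exposed beforehand, and use medicine count and Drug Burden Index as continuous measures. Keep the plain before-after and with/without tables as descriptive. Align the Sample size wording and the numbering of the objective.

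The cost is more programming on MBS and PBS data, which the Commonwealth datasets section says are already linked, and the loss of some recipients without a suitable comparator.

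### Aim 6 never sets the change in recipients of a medicines service against the change in non-recipients, and its detectable effect rests on before/after alone

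*Protocol article*

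**What the plan says.** The aim, listed sixth in the Background, is to "Investigate whether certain routine medicines-related interventions, including the Home Medicines Review and Chronic Disease Management are associated with reductions in high risk prescribing". The Statistical analysis section calls it the fifth objective and names two comparisons in one sentence. The first is between people: "we will compare the rates of high risk prescribing in participants with and without these interventions". The second is within people: "the incidence of high risk prescribing before and after each of these interventions, within individuals". Nothing in the section links them.

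The same section lists, for the project as a whole, "time-varying methods, and controlling for relevant confounding factors using a number of different approaches (eg. stratification by disease, propensity scores modelling"). None of these is tied to this aim.

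Under Sample size, with 5% exposed and a Beers prevalence of 20%, the article says "this would allow detection of a relative change in prevalence of 0.05", comparing before with after the intervention. No detectable effect is given for the with/without comparison.

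Under Health interventions, the Home Medicines Review follows a general practitioner's referral. Chronic Disease Management exists "to plan and coordinate the health care of patients with chronic or terminal medical conditions". No trigger for referral is stated.

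**The concern.** A within-person comparison removes confounders that stay fixed. It does not remove anything that would have changed over the same interval without the service. Two such changes are foreseeable. Medicine use rises with age, which would hide a benefit. If practitioners refer when medicine use is temporarily high, it then falls back by itself, which would imitate one.

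The with/without comparison does not resolve this, because it compares levels. People who are referred may start higher, so the service could look harmful there and helpful in the before/after result. Two contrasts with different biases do not correct each other. The aim asks about reductions, and the planned results could not separate a real reduction from background change.

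**Working it through.** **1. The plan's own figure.** Inputs: 73,528 concession card holders (45 and Up study cohort section); 5% exposed and 20% Beers prevalence (Sample size); 5% significance and 80% power, stated there for mortality and assumed to carry over, two-sided.

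- Exposed: 0.05 × 73,528 = 3,676. A relative change of 0.05 is 20% to 19%, or 1 percentage point.
- Treated as two independent samples, 20% v 19% needs 24,641 per group. With 3,676, power is 19% and the detectable relative change is about 13%.
- Treated as paired data, with d the proportion of people who change status and Δ the net change, n = [1.96√d + 0.84√(d − Δ²)]² / Δ². With n = 3,676, Δ = 0.01 is reached only if d is at most about 4.7%. At d = 10% the detectable change is 1.46 points, or 7% relative.

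The article gives no d, so 0.05 can be neither confirmed nor refuted. It serves here only as the size of effect sought.

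**2. Ageing (upward).** The Background puts polypharmacy at about half of people aged 65-74 and two-thirds of those aged 75 and over. The distance between the two bands is assumed to be 10-15 years.

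- Over 10 years: (0.667 − 0.50)/10 = 1.7 points a year; 1.7/50 = 3.3% relative a year.
- Over 15 years: 1.1 points a year, 2.2% relative a year.
- Time to reach 5% relative: 0.05 × 50 = 2.5 points, so 1.5 to 2.25 years, against a stated follow-up of 2-5 years. Over a six-month gap the drift is only 1.1-1.7%.

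**3. Regression to the mean (downward), with no true effect.** Assumed model: a normally distributed liability with threshold t = z(0.80) = 0.842 (20% prevalence). Recipients are shifted by s in the before window because of a temporary high, and a fraction ρ of that shift remains afterwards. After-prevalence = 1 − Φ(t − ρs). For an assumed 40% before, s = 0.842 − 0.253 = 0.588.

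| ρ | After (from 40%) | Relative change | Range for 30-60% before |
|---|---|---|---|
| 0.98 | 39.55% | −1.1% | −0.7% to −1.4% |
| 0.95 | 38.9% | −2.8% | −1.8% to −3.6% |
| 0.90 | 37.75% | −5.6% | −3.7% to −7.1% |
| 0.80 | 35.5% | −11.2% | −7.2% to −14.4% |

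A separate simulation, with 5% referred and referral odds rising 1.3- to 2.7-fold per SD of current liability, gives similar falls: 0-1.5%, 1.9-3.9%, 3.4-7.3% and 4.6-14.5% at the same four correlations.

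**4. Stable selection.** If recipients stand at 40% because of lasting illness, the simulated before/after change with no effect is zero at every correlation tried (0.95, 0.90, 0.80).

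**5. Choice of control.** In that stable-selection case, a difference in change against unmatched non-recipients is also about zero. Matching controls on the indicator in the two preceding windows instead gives a spurious relative rise of 6%, 9% and 14% at 0.95, 0.90 and 0.80. The matched controls are partly people who were temporarily high, and they fall back.

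**The case against.** The strongest reply is that the plan is brief rather than wrong. A with/without comparison stands in the same sentence, and time-varying methods and propensity scores are listed. A condensed article may leave the joining of the two comparisons to a fuller document. Age and calendar time could enter a within-person regression. Elsewhere the article discusses confounding by indication and warns against causal reading.

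Part of this stands. A reader might infer that aim 6 is judged only by an uncontrolled comparison; it is not. A reader might also infer that recipients are caught at a peak. The article says who refers, not when, and describes chronic conditions as present or likely to be present for at least six months, which fits stable selection at least as well. Nor does ageing alone reach 5% over short gaps. The age figures are cross-sectional and concern polypharmacy, while the 0.05 is set for Beers.

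What does not stand is that silence accounts for all of it. The article spells out the two contrasts for this aim and ties its only detectable effect to the one without a control. A propensity score needs an unexposed group, which the before/after contrast lacks. Adjusting for age and time would address drift but not regression to the mean. The Discussion mentions neither regression to the mean nor time trend.

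**Conclusion.** The concern holds in a limited form. As written, the before/after comparison for aim 6 is open to background change of a size comparable to the 5% relative effect sought: upward by about 2-3% a year (polypharmacy, with an assumed 10-15 years between age bands), and downward by about 1-14% if selection is on temporary highs (correlations 0.98-0.80, before-prevalences 30-60%, all assumed), or not at all if selection is on stable illness. The two run in opposite directions and may partly cancel, so the sign of the net bias is unknown.

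It would go too far to say that these artefacts must reach 5%: the documents give neither the prevalence among recipients nor the stability of prescribing status. The case for change is that the plan cannot tell which situation it is in, although a controlled contrast is available from data it already holds.

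**What to change.** Make the main aim 6 estimate the change in recipients minus the change over the same calendar period in concession card holders who have not (yet) had the service. Assign controls index dates, and adjust for or match on age, sex, calendar time and chronic disease markers. In addition:

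- Use several pre-index windows to check for parallel trends and for a peak before referral.
- Treat matching on the prior indicator value only as a sensitivity analysis, because it can itself induce regression to the mean (step 5).
- Report the uncontrolled before/after change as descriptive.
- Restate the detectable effect for the controlled contrast, giving the assumed proportion of people who change status.
- Use one number for this aim in the Background and in the Statistical analysis section.

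The cost is wording, programming and some precision; the PBS and MBS data are already linked for all participants. If all non-recipients serve as controls (about 19 per recipient) and change is equally variable in both groups, the standard error rises by √(1 + 1/19) = 1.026, or about 3%. With one control per recipient it rises by √2 = 1.41.
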